### **3.5. Subject Replacement**

Subjects who drop out will not be replaced.

## **4. TRIAL SCHEDULE**

1. Obtainment of ethical approvals from Domain Specific Review Boards (DSRB)
2. Signed research collaborative agreements between TTSH and NNI and separate service agreement with technical vendor.
3. Setting up of research accounts and codes and clinic code.
4. Clinical trial commences with face to face identification of suitable subjects from TTSH and NNI (TTSH) acute /rehabilitation wards and TTSH outpatient clinics.
5. Contact, eligibility screening, selection of eligible patients and informed consent process at the research sites at TTSH rehabilitation centre wards or clinics and /or TTSH-CART clinic 5B and subject will be enrolled on CDOC and assigned research code number.
6. NNI Neurosurgeon of study team will be informed of enrolled subjects' details to select suitable CT brain images.
7. These images will be sent to NNI Neuroradiology service staff for anonymisation of the selected CT brain scans.
8. Anonymised CT brain scans will be stored on CD-ROMS and labelled with assigned research code.
9. These will be transmitted to the vendor for segmentation and 3D printing.
10. 3D printed skull replacement piece will be labelled with research code and delivered in a sealed box to TTSH CART research site/TTSH Rehabilitation Centre and handed to a member of the study team for safe keeping under lock and key.
11. Research subject will be contacted for on-site physical visit for customisation of prosthesis fit with attachment of silicone padding to bony rim.
12. Assessment of fit on subject's skull by team and comfort of patient for first 30 minutes of donning.
13. If fit is deemed by study team to be not suitable, further 3D printing iterations as needed to improve customisation.
14. If suitable fit, integration to bony flap of patient with Velcro straps, elastic bands or caps.
15. Subject is monitored for first 30 minutes, educated by study coordinator or nurse in research clinic

site on donning, doffing, wearing schedule log, complications to look out for, monitoring and study visit schedule.

16. Subject brings HPPD home with supervision of NOK.
17. Outpatient monitoring phase for up to 8 weeks. (Follow up physical visits x 4 and phone calls x 3). If consented, photograph or videography may be used.
18. End of study at week 8 or earlier if has undergone cranioplasty.
19. Subject has option to retain his own HPPD if is comfortable wearing, has no adverse events, and is still awaiting or has refused cranioplasty.

## **5. STUDY DESIGN**

### **5.1. Summary of Study Design**

Study design is a pilot open label study with assessor measured outcomes. This study design is appropriate for the exploratory proof of concept study.

## **6. METHODS AND ASSESSMENTS**

1. Proof of Concept with open label pilot feasibility clinical trial.
2. Number of subjects to enrol: 10 (5 to 9 from TTSH and 1 to 5 from NNI)
3. Outpatient monitoring phase for up to 8 weeks (1 screening, 1 fitting, 4 follow up visits and 3 phone visits]
4. If planned cranioplasty is performed within 8 weeks of study inclusion, subject involvement will end on date of scheduled cranioplasty.
5. Assessments involve subjective evaluation of suitability of fit and complications during visits, patient and NOK log of duration of wearing and subjective complaints.
6. Digital photographs with pixilation of facial features or short video clips to document fit or outcome will be taken if subject consents. These may be used for education or safety review of the investigational product

### **6.1. Randomisation and Blinding**

As this is a feasibility pilot study using open label study design, there will no randomisation or blinding.

### **6.2. Contraception and Pregnancy Testing**

Reproductive age females should not be pregnant at the point of consent-taking and during the study.

### **6.3. Study Visits and Procedures**

Enrolled subjects will be required to visit the research site a total of ~6 times for 1.5 to 2 hours each time and undergo all trial procedures as stated below. (1 screening, 1 fitting, 4 follow up visits and 3 phone visits.

#### *a. Screening Visits and Procedures*

Visit 0: Screening for eligibility, explanation of clinical trial and informed consent process by patients/patient's LAR.

*b. Study Visits and Procedures*

Upon signing of informed consent, subject is recruited and enrolled on CDOC, the following processes will happen:

1. Identification and selection of suitable CT brain images (NNI Neurosurgeon)
2. Transmission of selected CT brain images to vendor for segmentation, processing, and 3D printing and packaging.
3. Delivery by vendor to research site (NNI/T\*TSH) and if preliminary fit is optimal, integration to subject skull defect with silicone padding and strapping to subject's scalp.
4. If non-optimal fit to patient as deemed by discomfort or observation of pressure signs after 30 minutes, further 3D printing iterations will be needed.
5. Subject education on donning/doffing, assessment of fit, cleansing, progressive wearing schedule and monitoring logs and study visit schedule as below.

*Study visit schedule:*

(Total of 6 physical visits (1 screening visit, 1 fitting visit, 4 follow up visits) and 3 phone call follow ups)

Visit 0: Screening for eligibility and informed consent process from patients'/patients' LAR.

Visit 1 (week 0): Fitting of HPPD and integration and adjustments as needed, education on donning and doffing, device care and cleaning, scalp care, (written instructions will be provided, progressive wearing schedule and monitoring logs). If consented, photography or videography may be performed to document progress at physical visits. Subject will be issued with HPPD to bring home to adapt to it.

Visit 1.1: Follow up telephone call on day 1 after visit 1 from study coordinator.

Visit 1.2: Follow up telephone call 3 days after visit 1.1 from study coordinator.

Visit 2 (end Week 1): Outpatient follow-up review and questionnaires by study coordinator.

Visit 3 (end week 2): Outpatient follow-up review and questionnaires by study coordinator.

Visit 4 (end week 4): Outpatient follow-up review and questionnaires by study coordinator.

Visit 4.5 (end week 6): Follow up telephone call on week 6 from study coordinator.

Visit 5 (week 8): *Final study visit:* Outpatient follow-up review and questionnaires by study coordinator. \*

End of Study (week 8 or earlier if subject undergoes cranioplasty)

*\* (if subject is scheduled for cranioplasty earlier than any of the scheduled study visits, their participation will end on the date of scheduled cranioplasty)*

\*\* Contingency plan for Covid 19: Additional post week 8 Phone follow-up x1 by study coordinator if subject has not received cranioplasty by end week 8 follow up. (study amendment submitted 22 Aug 2020)

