## **2.1. Hypothesis**

Our primary hypothesis is that 80% of subjects will be safely fitted with head protection prototype devices (HPPD) without immediate complaints of pain or discomfort or signs of bony defect scar pressure or redness or wound breakdown within the first 2 hours in the research clinic.

Our secondary hypothesis is that 70% of these subjects will be without complaints of pain or discomfort or signs of bony defect scar pressure or redness or wound breakdown in the first week of outpatient monitoring.

In addition, subjects will tolerate HPPD wear progressively up to 8 weeks for specified high risk activities.

We anticipate a 25% dropout rate at 8 weeks.

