### **3.3. Inclusion Criteria**

All subjects must meet all of the inclusion criteria to participate in this study.

1. Age 21 to 80 years, both males and females.
2. Presence of surgical unilateral or bilateral craniectomy performed for reasons of ischaemic or haemorrhagic stroke, Subarachnoid haemorrhage (SAH), traumatic brain injury (TBI), benign cerebral tumours, etc.
3. Stroke, SAH or TBI are diagnosed by specialists and confirmed on brain imaging studies (CT, MRI)
4. Duration from event > 30 days and either during inpatient or outpatient phase.
5. Presence of at least 1 post decompressive craniectomy CT brain film performed at NNI/TTSH.
6. Healed craniectomy surgical wound without bulging skin flap or active skin infection.
7. Patients awaiting elective cranioplasty or those who refuse cranioplasty.
8. Ability to understand simple instructions.
9. Presence of family members or NOK who can supervise the patient to don the head protection device, care for the material and regularly monitor for compliance and complications.
10. Reproductive age females should not be pregnant at the point of consent-taking and during the study.

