#### *Exclusion Criteria*

All subjects meeting any of the exclusion criteria at baseline will be excluded from participation.

1. Patient in vegetative or minimally responsive state.
2. Presence of uncontrolled medical condition (uncontrolled hypertension, Diabetes Mellitus, sepsis or delirium, active malignancy either cranial or extracranial sites)
3. Presence of end organ failure (end stage renal or liver failure, renal dialysis, life expectancy <6 months)
4. Presence of pregnancy or lactation.
5. Presence of severe agitation /behavioural/active depression or anxiety/ drug or alcohol addiction which would negatively affect compliance,
6. Presence of unhealed head wound, active wound infection, scalp dermatitis, wound breakdown which would be worsened by pressure from the HPPD.
7. Presence of known allergy to the investigational products which is the 3D printed material (e.g. Nylon).
8. Subjects' CT brain imaging films are not available to the study team.

9. Absence of NOK who can assist monitoring unless subject is able to self-monitor.

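### No pain, redness or pressure-mark record is listed just before first donning, and the 2.1 criteria are not limited to new or worsened findings

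*Protocol*

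**What the plan says.** Section 2.1 states the primary hypothesis as "80% of subjects will be safely fitted with head protection prototype devices (HPPD) without immediate complaints of pain or discomfort or signs of bony defect". The signs it goes on to name are pressure on the scar, redness and breakdown of the wound, all counted over the first 2 hours in clinic. The secondary hypothesis, for the first week, is that "70% of these subjects will be without complaints of pain or discomfort", and the same scar and wound signs apply. Neither asks whether the finding was there before the device was worn.

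In 6.3, Visit 0 consists of eligibility and consent. The next physical visit is "Visit 1 (week 0): Fitting of HPPD and integration and adjustments as needed", followed by education and issue of the device. Section 4 (items 11 to 15) runs in the same order. The subject attends for customisation, the team assesses fit and "comfort of patient for first 30 minutes of donning", and the device is then integrated and the subject monitored and taught. The pressure-sign check that can trigger a reprint (6.3 b, item 4) also follows 30 minutes of wear.

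Scalp status is addressed at entry. Inclusion criterion 6 requires "Healed craniectomy surgical wound without bulging skin flap or active skin infection". Exclusion criterion 6 bars unhealed wounds, wound infection, scalp dermatitis and breakdown that device pressure would worsen, under the rule "All subjects meeting any of the exclusion criteria at baseline will be excluded from participation". Photographs at physical visits depend on consent. The study schedule, the screening form and the data collection form are listed as attachments and are not shown.

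**The concern.** The study has one arm, is open label and has no control, so the subject's own state before donning is the only reference for what the device did. Four of the five components of the criterion (pain, discomfort, pressure sign, redness) can exist before fitting in an eligible subject. Entry is possible from just over 30 days after the event, and no criterion mentions pain, or redness short of infection or dermatitis.

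The error can run in either direction. Read literally, a scar that was already red, or a headache the subject always has, is a failure of the device. If an assessor instead uses judgement and has no record to judge against, redness caused by the device may be put down as old. In a first-in-human study the second error matters more, because it hides harm. Either way, the two proportions would not cleanly describe the device.

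**Working it through.** The protocol gives no sample size derivation, error rate or power (11.1), so there is no planned figure to reproduce. The check has two parts.

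**1. Criterion against entry screen and visit content**

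| Component in 2.1 | Covered by entry criteria? | Listed check before donning at Visit 1? |
|---|---|---|
| Pain | No | None listed |
| Discomfort | No | None listed |
| Scar pressure sign | No | None listed |
| Redness | Only as infection or dermatitis | None listed |
| Wound breakdown | Yes, at screening | None listed |

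Image selection, anonymisation, printing and delivery lie between screening and fitting. The interval is not stated.

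**2. Size**

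Inputs: n = 10 (3.1); targets 80% and 70% (2.1). The number or rate of subjects with a pre-existing finding is not in the documents and is assumed. Reading the targets as 8 of 10 and 7 of 10 is also an assumption.

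*Each subject:* 1/10 = 10 percentage points. 80% of 10 is 8, so 2 failures are compatible with the target.

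*A device that causes no problem,* with k subjects whose prior findings count as failures, scores (10 − k)/10:

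- k = 1: 90%
- k = 2: 80%
- k = 3: 70%, below 80%

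*A device with a true device-only success rate p,* with prior findings at rate b independent of the device, has an observed success rate of p(1 − b). For example, 0.80 × (1 − 0.10) = 0.72. The binomial chance of reaching the target count with n = 10 is then:

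| b (assumed) | Primary: 0.80(1 − b) | P(at least 8/10) | Week 1: 0.70(1 − b) | P(at least 7/10) |
|---|---|---|---|---|
| 0% | 80% | 0.678 | 70% | 0.650 |
| 5% | 76% | 0.556 | 66.5% | 0.555 |
| 10% | 72% | 0.438 | 63% | 0.460 |
| 20% | 64% | 0.241 | 56% | 0.288 |
| 30% | 56% | 0.111 | 49% | 0.156 |

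The opposite error, a device finding dismissed as old, raises the observed rate by the same 10 points per subject.

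**The case against.** Four arguments weigh against the point.

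- **The forms are not shown.** A reader might infer that no baseline of any kind is taken. The documents do not support that. The wound is screened at entry, and the screening form, data collection form and study schedule may contain pain or scalp items. What stands is that the visit procedures, as written, list none before donning. A baseline item on a form would also not help while the criterion in 2.1 ignores it.
- **The protocol expects clinical judgement.** A reader might infer that a wound that deteriorated after screening would go unnoticed, or that old findings could never be separated from device effects. That is too strong. The safety end points in 2.4 b include being unable to fit a subject safely because of wounds, and complications attributed to the device or its straps. The withdrawal criteria speak of new scar infection and of reactions attributed to the device, and the team handles the scalp in person at fitting. What stands is that attribution without a pre-donning record is less reliable, and that the 2.1 criteria carry no such attribution or novelty wording.
- **Counting every finding is a defensible, conservative tolerability measure.** This is fair. Restricting to new or worsened findings is more lenient and measures something different, so both rates should be reported.
- **The magnitude is assumed and the study is imprecise.** Also fair. The exact 95% interval for 8/10 is about 44% to 97%, and the protocol states hypotheses without a formal success rule. A reader might infer that prior findings would make the trial fail. The documents support only that they would shift the reported proportions.

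**Conclusion.** The point holds as a cheap improvement to the design, not as an error of calculation. The listed procedures contain no recorded assessment of pain, discomfort, redness or pressure marks just before first donning, and the primary and secondary criteria are not limited to new or worsened findings. Pre-existing findings therefore cannot be reliably told from device effects. To say that they can never be told apart would go further than the documents allow.

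Each misattributed subject shifts the result by 10 percentage points. The 90% to 70% range for a harmless device rests on an assumed 1 to 3 of 10 subjects with prior findings. The probabilities rest further on independence and on reading the targets as 8 and 7 of 10. These figures are illustrative. The conclusion itself depends only on the wording of 2.1, the entry criteria and the visit list, with the reservation that the unseen forms may already collect part of what is needed. An analysis plan cannot repair this later if the baseline was not collected.

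**What to change.** 1. At Visit 1, just before donning, have the staff already present record scar and rim redness, skin integrity and a 0-10 pain/discomfort rating on the data collection form. If the existing forms already capture these items at that moment, say so in 6.3 instead.
2. In 2.1, define both criteria as freedom from new or worsened pain, discomfort, scar pressure sign, redness or wound breakdown compared with that record.
3. Score later visits against the same record.
4. Also report the proportion with any finding regardless of baseline, at 2 hours and at week 1.

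Cost: one block on a form, a few minutes at an existing visit and a wording change in 2.1, with no added visit or staff. The criterion becomes slightly more lenient, which the any-finding rate makes visible.

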### *Post Study Follow up and Procedures*

1. HPPD is returned to study coordinator if subject has undergone cranioplasty.
2. On CDOC, subject status is updated to “disenrolled”
3. Outcomes on data collection form are completed and data converted to electronic copies in password protected desktop computers.
4. Study team meets after every 5 subjects enrolled to evaluate HPPD subject response, adverse events and outcome.

#### *a. Discontinuation Visit and Procedures*

Subjects may withdraw voluntarily from participation in the study at any time. Subjects may also withdraw voluntarily from receiving the study intervention for any reason.

In the event of a withdrawal due to adverse event (i.e. skin breakdown), subject will immediately discontinue application of the HPPD, be given appropriate care under medical supervision until the symptoms of any adverse event resolve or the subject’s condition becomes stable and subject should complete an end of study evaluation.

In the event of acute unrelated medical decompensation requiring hospitalisation, subject will cease wearing schedule for HPPD till recovered. Subject will be monitored for fitness to continue study and monitoring visits, unless eligibility criteria have changed which exclude subject from participation. (e.g. subject becomes unable to understand simple instructions, vegetative state, severe wound status, terminal medical condition with life expectancy < 6 months.

If the withdrawal is voluntary and not due to an adverse event such as skin breakdown or discomfort, subject should return the HPPD, and monitoring visits and wound management will continue till skin healed.

## **7. TRIAL MATERIALS**

### **7.1. Trial Product (s)**

The proposed HPPD uses biocompatible material using FDM Nylon which has high fatigue resistance, chemical resistance with impact resistance and toughness which is free of powders. 12 Model Material. (please refer to 2 attached references from vendor)

### **7.2. Storage and Drug Accountability**

Prostheses will be stored in a provided sealed clear box in a locked cupboard at room temperature (< 55dC) and humidity with subject code label.

## **8. TREATMENT**

### **8.1. Rationale for Selection of Dose**

Not applicable

### **8.2. Study Drug Formulations**

Not applicable.

### **8.3. Study Drug Administration**

Not applicable.

### **8.4. Specific Restrictions / Requirements**

There are no limitations on medications, herbs, vitamins and mineral supplements (while participating in the study) and there will be no alterations or restrictions to subjects' pre-existing or concurrent medication.

### **8.5. Blinding**

Not applicable (see 6.1)

### **8.6. Concomitant therapy**

There will be no alterations or restrictions to subjects' pre-existing or concurrent therapies whether related to medication, rehabilitation, complementary or alternative therapies medication.

## **9. SAFETY MEASUREMENTS**

### **9.1. Definitions**

Define terms e.g. what would be regarded as UPIRTSO events, Serious adverse events etc.. Include details of the protocol specific reporting, procedures, including the individual responsible for each step (e.g. the Investigator, the medical monitor, etc.), how decisions will be made regarding determining relatedness and grading severity, how reports will be distributed and what follow up are required. Include specific details of reporting procedures for:

- Deaths and life-threatening events
- other SAEs
- Other adverse events

### **9.2. Collecting, Recording and Reporting of "Unanticipated Problems Involving Risk to Subjects or Others" – UPIRTSO events to the NHG Domain Specific Review Boards (DSRB)**

**UPIRTSO events** refers to problems, in general, to include any incident, experience, or outcome (including adverse events) that meets ALL of the following criteria:

**1. Unexpected**

In terms of nature, severity or frequency of the problem as described in the study documentation (eg: Protocol, Consent documents etc).

**2. Related or possibly related to participation in the research**

Possibly related means there is a reasonable possibility that the problem may have been caused by the procedures involved in the research; and

**3. Risk of harm**

Suggests that the research places participants or others at a greater risk of harm (including physical, psychological, economic, or social harm) than was previously known or recognized.

**Reporting Timeline for UPIRTSO Events to the NHG DSRB.**

1. Urgent Reporting: All problems involving local deaths, whether related or not, should be reported immediately – within 24 hours after first knowledge by the NHG investigator.
2. Expedited Reporting: All other problems must be reported as soon as possible but not later than 7 calendar days after first knowledge by the NHG investigator.

**9.3. Collecting, Recording and Reporting of Serious Adverse Events (SAEs) to the Health Science Authority (HSA)**

**1. For Industry sponsored Trials**

All SAEs will be reported to HSA according to the HSA Guidance for Industry “Safety Reporting Requirements for Clinical Drug Trials.”

**2. For Principal Investigator initiated Trials**

All SAEs that are unexpected and related to the study drug must be reported to HSA.

“A serious adverse event or serious adverse drug reaction is any untoward medical occurrence at any dose that:

- Results in death.
- Is life-threatening (immediate risk of death).
- Requires inpatient hospitalization or prolongation of existing hospitalization.
- Results in persistent or significant disability/incapacity.
- Results in congenital anomaly/birth defect.
- Is a Medically important event.

Medical and scientific judgment should be exercised in determining whether an event is an important medical event. An important medical event may not be immediately life threatening and/or result in death or hospitalization. However, if it is determined that the event may jeopardize the subject and/or may require intervention to prevent one of the other adverse event outcomes, the important medical event should be reported as serious.”

All SAEs that are unexpected and related to the study drug will be reported. The investigator is responsible for informing HSA no later than 15 calendar days after first knowledge that the case qualifies

for expedited reporting. Follow-up information will be actively sought and submitted as it becomes available. For fatal or life-threatening cases, HSA will be notified as soon as possible but no later than 7 calendar days after first knowledge that a case qualifies, followed by a complete report within 8 additional calendar days.

